### Outcome measures

3.3

#### Primary outcome

3.3.1

Disease outcomes include cure, significant effect, effective, and ineffective. The main result is the total clinical effectiveness after treatment (day 14) of the 2 groups, that is, the sum of cure rate, apparent efficiency and effective.

#### Secondary outcomes

3.3.2

1)**TCM symptom score scale (**at days 4, 8, and 14).2)**Pneumonia severity index** (at days 4, 8, and 14).3)**usage time of antibiotic** (at days 6, 10, and 14).4)**time required for blood sugar to reach the required level (**at days 2, 4, 6, 8, 10, 12, 14).5)**frequency of hypoglycemia (**at days 2, 4, 6, 8, 10, 12, 14).6)**laboratory examination:** including white blood cell count, percentage of neutrophils, C-reactive protein and procalcitonin **(**at days 4, 8, 14).7)**chest CT (**at days 14).8)** Exploratory outcome:** Differences in blood metabolomics between the 2 groups after treatment **(**at days 14).

### Safety assessment

3.4

The dose of modified BXXXD used in this study is within the recommended range based on the People's Republic of China Pharmacopeia (2015 edition). Furthermore, we take a variety of measures, including laboratory tests and subjective descriptions to evaluate the presence of gastrointestinal intolerance and liver or kidney dysfunction.

### Compliance

3.5

Once subjects are randomized, investigators will try to follow them throughout the study. At each visit, adherence to intervention are monitored and subjects are required to return all unused packs of granules. Furthermore, subjects will be served with continuous support in subsequent stages, such as post-discharge rehabilitation advice.

### Adverse events

3.6

Adverse events are defined as unanticipated or negative clinical features following treatment. Subjects are required to inform investigators of any abnormal reactions during the trial. In case of any severe adverse events, the intervention will be stopped immediately and a detailed description of severity, time, relationship with the drug, and the measures adopted derived from standard operational procedures of the China Food and Drug Administration will be recorded detaily in CRFs.

### Data management and quality control

3.7

The researches in the study team have been asked for attending a training seminar before recruitment. Each one obtains a copy of the study protocol and they are required to comply with the protocol throughout the study period.

All data are recorded and gathered on CRFs. Any corrections or changes to the data written in CRFs should be documented and dated. All records are entered into a password-protected and pre-designed database by administrators who are blind to the group assignment. Two data administrators input and proofread the data independently to ensure the accuracy of the data. In addition, the Sichuan TCM evidence-based medicine center (Chengdu, China), which has no competitive interest, will be in charge of monitoring the data. The Department of Science Research of Affiliated Hospital of Chengdu University of TCM, which is independent of the research team, will perform data audits during the trial.

### Statistical analysis

3.8

Statistical analysis will be performed at the Sichuan evidence-based Medicine Center of TCM using Statistical Package for the Social Sciences version 22.0 (SPSS 22.0, Chicago, IL). Intention-to-treat and per protocol sets are applied to analyse the efficacy of modified BXXXD. A safety analysis set is used to assess the safety of the study. Missing values are estimated using the principle of the last observation carried forward, with the data from the last study follow-up used as the final results.

Categorical data are tabulated with frequencies or percentages, and continuous data are reported as median or mean ± standard deviation. For the sociodemographic data and baseline variables are conducted using analysis of variance and Chi-squared test. To compare the variables of the same group before and after treatment, a paired *t*test is used. Repeated measures analysis of variance is used to compare the differences among the 2 groups. All statistical tests are bilateral tests and *P* values < .05 is regarded as statistical significance.

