**Methods::**

We propose a double-blind, placebo-controlled, randomized superiority trial.

A total of 92 participants with T2DM-CAP will be randomly allocated at a 1:1 ratio to either the experimental group, which will receive modified Ban-Xia-Xie-Xin-Decotion and basic treatment, or the control group, which will receive basic treatment only. The study duration will be 14 days. The primary outcome will be the total clinical effective rate. The secondary outcomes are traditional Chinese medicine symptom score scale, pneumonia severity index, usage time of antibiotic, time required for blood sugar to reach the required level, frequency of hypoglycemia, and chest CT. Liquid chromatograph-mass spectrometry method will be used to explore the blood metabolism profiles of the subjects, to explore the pathogenesis of T2DM-CAP and the mechanism of CHM on T2DM-CAP. Adverse events will also be evaluated.

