### Sample size

2.4

Sample size calculations are based on the primary outcome (the clinical effective rate at 2 weeks). According to the previous literature,^[34]^ we assumed the clinical effective rate of 73% in the control group and 93% in the experimental group over 14 days. Thus, a sample size of 82 patients is needed to achieve a statistical power of 80% (single-sided type-1 error of 5% in both scenarios). Assuming that 10% of patients are likely to be lost during follow-up, a total of 92 patients will be enrolled.

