### Termination and withdrawal criteria

2.10

All participants are informed of their right to terminate and withdraw from the trial. The reason will be recorded in case report forms (CRFs). The criteria for stopping treatment and withdrawing from the research are:

participants suffered severe adverse reactions related to the medication, and the researcher believes that they should stop taking drugs;participants suffered from another serious illness that required treatment during the study;participants’ condition deteriorate severely and even require respiratory support therapy;poor compliance, the actual dose is less than 80% of the prescribed dose.

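### The blanket last-observation-carried-forward rule also covers hypoglycaemia frequency, an event count with no persisting value to carry forward

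*Protocol article*

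**What the plan says.** Section 3.8 (Statistical analysis) gives a single missing-data rule: "Missing values are estimated using the principle of the last observation carried forward, with the data from the last study follow-up used as the final" [...]. It names no outcome and makes no exception. The same section names repeated measures analysis of variance for comparing the two groups and mentions no exposure or time-at-risk term.

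Section 3.3.2 (Secondary outcomes) lists "frequency of hypoglycemia (at days 2, 4, 6, 8, 10, 12, 14"), which is seven records two days apart. It does not say whether each record counts episodes since the previous one or since the start.

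Early exit is expected. Section 2.4 (Sample size) reads "Assuming that 10% of patients are likely to be lost during follow-up, a total of 92 patients will be enrolled". Section 2.10 (Termination and withdrawal criteria) covers both stopping treatment and leaving the research. Its reasons include "participants suffered severe adverse reactions related to the medication, and the researcher believes that they should stop taking drugs", a "condition deteriorate severely and even require respiratory support therapy", another serious illness, and "poor compliance, the actual dose is less than 80% of the prescribed dose".

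**The concern.** Carrying a value forward presumes a state that plausibly continues, such as a symptom score. A count of episodes is not a state. It accrues over time at risk, and its natural denominator is the time the patient was observed. The stated rule therefore does one of two things to a patient who leaves early. It repeats the last interval's count in intervals nobody observed, or it freezes a running total and treats unobserved days as free of episodes.

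At stake is the frequency reported in each arm for the only hypoglycaemia outcome listed, in patients who all receive glucose-lowering treatment. If exits differ between arms, the comparison could be affected too. Repairing the rule for the day-14 response or for durations would not repair this count, which needs observed time as its denominator.

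**Working it through.** **Inputs from the protocol article.** Records at days 2, 4, 6, 8, 10, 12 and 14, so 7 two-day windows (3.3.2). Planned loss 10%, and 92 enrolled 1:1, so 46 per arm (2.1, 2.4). The loss figure reproduces the enrolment: 82 / (1 - 0.10) = 91.1, rounded up to 92. No hypoglycaemia figure is given, so there is none to reproduce.

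**Assumptions, not in the article.** 0.5 episodes per patient per 14 days (range 0.3 to 1.0), Poisson counts, and leaving spread evenly over the records at days 2 to 12.

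**One patient: one episode on days 5-6, leaves at day 6.**
- Per-interval record: the value 1 is repeated at days 8, 10, 12 and 14. Total = 1 + 4 = 5, against 1 observed.
- Cumulative record: the total 1 stands for 14 days. The rate is 1/14 instead of 1/6 per day, a ratio of 6/14 = 0.43, so 57% too low. Unobserved days counted as event-free: 14 - 6 = 8.
- Under a constant rate the per-interval rule is unbiased on average for a day-6 leaver. The variance of the filled-in total is still [2 + (1 + 4)²] / 7 = 27/7 = 3.9 times that of a complete 14-day count.

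**One arm, cumulative reading.** Leavers contribute on average 3.5 of 7 windows.
- 10% loss: 0.90 + 0.10 × 0.5 = 0.95, so 5% too low.
- 20% loss: 0.80 + 0.20 × 0.5 = 0.90, so 10% too low.

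**One arm, per-interval reading, 10% loss.** Leavers: 46 × 0.10 = 4.6, with 3.5 missing windows each, so 16.1 filled-in windows. Mean per window: 0.5/7 = 0.0714. Chance of no episode in a window: exp(-0.0714) = 0.931. A fraction q of leavers is given at least one episode in the last record, so that record has mean 0.0714 + 0.931q. Observed episodes are 46 × 0.5 × 0.95 + 4.6 × 0.931q. The benchmark is the rate per observed day scaled to 14 days, which is observed episodes / 0.95.

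| q | Observed | Added by the rule | Filled-in total | Benchmark | Excess |
|---|---|---|---|---|---|
| 0 | 21.9 | 1.2 | 23.0 | 23.0 | about 0 |
| 1/4 | 22.9 | 4.9 | 27.8 | 24.1 | 15% |
| 1/2 | 24.0 | 8.6 | 32.6 | 25.3 | 29% |

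For q = 1/4 the excess is 25% at 0.3 episodes per patient and 7% at 1.0. If exactly a quarter or half of leavers, background included, have an episode in the last record, the excess is about 12% or 27%.

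**Between arms, no true difference.** Simulation with 46 per arm, 0.5 episodes per patient, and a two-sided 5% t-test on patient totals (the between-group test of a repeated measures analysis of variance). False-positive rates:

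| Loss by arm | Leavers given an episode | Per-interval | Cumulative |
|---|---|---|---|
| 10% v 10% | none, 1/4 or 1/2 | about 4.5% | about 5% |
| 15% v 5% | none | about 5% | about 5% |
| 15% v 5% | 1/4 | 6% to 7% | about 5% |
| 15% v 5% | 1/2 | about 11% | 5% to 6% |

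Under the cumulative reading, 15% v 5% loss unrelated to episodes gives a ratio of means of (1 - 0.075) / (1 - 0.025) = 0.95 where the truth is 1. That is a bias in the estimate, too small against the noise to move the error rate much.

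**The case against.** The strongest reply is that the comparison is hardly affected. Under the plan's own 10% loss, split equally, the errors cancel between arms and the false-positive rate stays near 5%. Distortion of the test needs unequal loss together with leaving tied to episodes. Nothing in the article supports a quarter or half of leavers having an episode in their last record: at 0.5 episodes per patient the background chance is about 7%. Section 2.10 does not name hypoglycaemia as a reason for withdrawal, although a severe episode might count as a severe drug-related reaction. All of this stands, and it limits the size of the point.

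A reader might infer that hypoglycaemia is the trial's main glucose-safety comparison, and that a handful of carried-forward values can decide it. The article supports neither. Section 3.3.2 lists the outcome fifth among the secondary outcomes, section 3.4 names gastrointestinal intolerance and liver or kidney dysfunction, and the error rates above show no such effect under equal loss.

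Section 3.5 says investigators will try to follow everyone randomised. That may reduce the missing data, but section 2.10 still provides for leaving the research.

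Finally, a condensed article may leave the recording of episodes and the choice of count model to a fuller document. That is fair, and neither gap is the finding. The finding is the stated rule: it is unqualified, and it fails under either way of recording.

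**Conclusion.** The point holds as a wrong stated rule for one secondary outcome, of minor-to-moderate weight. The patient-level error follows from the rule alone: 5 episodes for 1, or a rate 57% too low, for the day-6 leaver.

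The arm-level sizes rest on the assumed episode rate and timing of leaving. The cumulative figure needs nothing further. The 15% and 29% figures also need leaving to be related to episodes, and without that the per-interval mean is about unbiased, though noisier. The between-arm test is distorted mainly when loss differs by arm and, for per-interval records, is related to episodes. In the case examined the false-positive rate was then about 7% to 11%.

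**What to change.** In section 3.8, exempt hypoglycaemia frequency from last observation carried forward and from repeated measures analysis of variance. Analyse the number of episodes per patient with a negative binomial model (or Poisson with robust errors), with the log of days actually observed as offset. Report the rate ratio with its 95% confidence interval, and the number of patients in each arm with at least one episode.

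State that this rate assumes leaving is unrelated to episodes, and report exits by arm and reason. The caveat is needed because the observed-days rate is not immune. In the scenarios above it is 24.1/46 = 0.525 or 25.3/46 = 0.55, against an assumed 0.50, so about 5% or 10% too high.

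The cost is a few sentences, one extra model and a somewhat wider interval than filled-in data would show. The two-day records already give the observed days, so no new data are needed.

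### Last observation carried forward is poorly defined for the day-14 primary outcome and can count participants withdrawn for deterioration or severe drug reactions as treatment successes

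*Protocol article*

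**What the plan says.** Section 3.8 (Statistical analysis) of the protocol article gives one rule for missing data: "Missing values are estimated using the principle of the last observation carried forward". It makes no exception for the primary outcome or for the reason a value is missing. The value that counts at the end is also fixed there: "with the data from the last study follow-up used as the final results".

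Section 2.10 (Termination and withdrawal criteria) introduces its list with "The criteria for stopping treatment and withdrawing from the research are", so these participants leave the study and not only the granules. The list covers cases where "participants suffered severe adverse reactions related to the medication" and cases of "condition deteriorate severely and even require respiratory support therapy". It also includes a new serious illness and poor compliance.

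Section 3.3.1 (Primary outcome) sets the endpoint and its timing: "The main result is the total clinical effectiveness after treatment (day 14) of the 2 groups". The grades are given as "Disease outcomes include cure, significant effect, effective, and ineffective", and the first three are added together as success. Nothing there assigns a participant withdrawn for deterioration to the ineffective grade.

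Section 3.3.2 (Secondary outcomes) schedules the symptom score, the pneumonia severity index and the laboratory tests "at days 4, 8, and 14". It lists no earlier visit for the effectiveness grade.

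**The concern.** In a two-week pneumonia trial, a participant who leaves because the illness worsens severely is a treatment failure, and one who leaves because of a severe drug reaction is an informative loss. Carrying forward the last value assumes that the status before leaving would have held to day 14. For these participants the reason for leaving contradicts that assumption.

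The rule also fits the endpoint badly. With the grade scheduled only at day 14, there are two possibilities:

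- There is no earlier grade, so the rule yields nothing.
- Someone derives a grade from day 4 or day 8 components, and a participant who looked better on day 8, worsened on day 10 and was withdrawn is scored from day 8.

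At stake is the intention-to-treat result of a 92-patient trial in which, at the planned 10% loss, 0.10 × 46 = 4.6 participants per arm depend on the imputation rule.

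**Working it through.** **Inputs.** From section 2.4: effective rates of 73% (control) and 93% (experimental), 82 patients needed, 10% loss, 92 enrolled, 80% power, one-sided 5%. From section 3.8: two-sided tests at 5%. With 1:1 allocation, 92 patients give 46 per arm. The number of withdrawals for deterioration or drug reaction is not given, so every misclassification fraction below is an assumption.

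**The plan's own figure.** With unpooled variance and one-sided 5%, n per arm = (0.73×0.27 + 0.93×0.07) × (1.645 + 0.842)² / 0.20² = 0.2622 × 6.183 / 0.04 = 40.5, rounded up to 41. The total is 82, and 82/0.90 = 91.1, rounded up to 92. Both figures reproduce.

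**Baseline for the illustration.** Power is computed exactly from the binomial distributions, with a two-sided 5% chi-square test without continuity correction at 46 per arm. At 73% vs 93% it is 76.7%. This differs from the plan's 80% because that figure is one-sided and uses 41 per arm.

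**A: the same fraction f of failures in each arm is scored effective.** The observed rate is q = p + f(1 − p).

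| f | Control | Experimental | Difference | Power |
|---|---|---|---|---|
| 0 | 73.0% | 93.0% | 20.0 points | 77% |
| 1/3 | 0.73 + 0.27/3 = 82.0% | 0.93 + 0.07/3 = 95.3% | 13.3 points | 57% |
| 1/2 | 0.73 + 0.27/2 = 86.5% | 0.93 + 0.07/2 = 96.5% | 10.0 points | 45% |

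Plausibility against the planned 10% loss:

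- f = 1/3 means 9.0% of the control arm and 2.3% of the experimental arm are withdrawn and misclassified, or (9.0 + 2.3)/2 ≈ 5.7% overall.
- f = 1/2 means 13.5% and 3.5%, or 8.5% overall. That is close to the whole planned loss, and in the control arm it exceeds 10%.

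**B: the same absolute proportion in each arm.** With 5% in each, 73 + 5 = 78% vs 93 + 5 = 98%. Both rates are too high, but the difference stays at 20 points.

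**C: more in the control arm.** With 10% control and 5% experimental, 83% vs 98%, a difference of 15 points.

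**D: upper limit in the experimental arm.** At the planned 93% only 100 − 93 = 7% are failures, so misclassification can add at most 7 points there.

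**E: no true effect, 73% in both arms.**

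- 10% misclassified in the experimental arm alone gives 83% vs 73%. The chance of a significant result favouring that arm is about 21%, against a nominal 2.5%.
- 10% experimental and 5% control gives 83% vs 78%, and the chance is about 9%.

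**The case against.** The strongest reply is that the misclassification is not certain. Participants are inpatients at entry, reasons for withdrawal go into the case report form, and section 3.5 says investigators will try to keep following everyone randomized. If the last follow-up is made at withdrawal, after the deterioration, carrying it forward gives the ineffective grade. This stands as a limit: the article neither requires nor excludes such an assessment. The point is therefore that a failure can count as effective, not that it will.

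It can also be said that the text shows an undefined rule more firmly than a quantified bias, because no earlier effectiveness grade is scheduled. That is fair. The grading criteria are not in the article either, and the full protocol may already class deterioration as ineffective. But a rule that is either empty or contradicted by later events still needs replacing.

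The fractions of one third and one half have no source in the document. The first stays well inside the planned loss overall; the second is near a worst case.

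The separate analysis plan is no answer to the main point. The article does not defer the missing-data method; it states one. The planned per-protocol analysis is no cure for informative withdrawal.

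**Conclusion.** The concern holds in a limited form. As written, the missing-data rule is poorly defined for the primary outcome and can count outcome-related withdrawals as successes, provided no assessment after the event is recorded and an earlier grade is derived. Effective rates can then be too high. The difference can shrink, grow or stay the same, depending on how misclassification divides between the arms. Under the assumed one-third fraction, 20 points become 13 and power falls from 77% to 57%. With no true effect and 10% misclassified in the experimental arm alone, the chance of a false positive in its favour is about 21%.

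The documents do not support several stronger readings that a reader might infer:

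- **That the intention-to-treat result is biased for certain, or in a known direction.** Equal absolute misclassification leaves the difference at 20 points.
- **That the experimental rate could be inflated by 10 points under the planning assumptions.** At 93% the ceiling is 7; 10 points requires a lower true rate, as in the case of no effect.
- **That the secondary scores and laboratory values are shown to be harmed.** The argument concerns the primary outcome only.

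**What to change.** Do not use last observation carried forward for the primary outcome. For the intention-to-treat analysis, state before unblinding:

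1. Participants withdrawn before day 14 for deterioration, respiratory support, a severe drug reaction or death count as ineffective.
2. Day-14 status is used where it is obtained. Say in advance which rule prevails for a participant to whom both this and the first apply.
3. Other missing outcomes, including those after withdrawal for an unrelated illness, are handled by multiple imputation. Counting every such illness as failure would be a debatable choice of estimand and is not needed here.
4. A best/worst-case or tipping-point analysis shows how far the conclusion depends on the imputed outcomes.

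The cost is a change of wording and a little more analysis. Both effective rates will look somewhat lower. The sample size stays at 82 evaluable and 92 enrolled, provided the planning rates of 73% and 93% are taken to count such withdrawals as failures.

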### Recruitment

2.3

All patients with T2DM-CAP at endocrinology department and respiratory department in hospital of Chengdu University of Traditional Chinese Medicine (TCM) (Chengdu, China) will be screened and enrolled. Prior to enrollment, subjects will be informed about the detailed explanation of the clinical study, including the purpose, scheduling, and possible benefits and risks. All eligible participants will be required to sign an informed written consent before the start of the study process. Patient recruitment starts in August 2020 and is planned to be completed in August 2021.

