### Randomization and allocation concealment

2.5

A member of Sichuan evidence-based Medicine Center of TCM, who does not participate in subsequent trials, uses SAS 9.2 software (SAS Institute Inc., Cary, NC) to generate 92 random serial numbers. Randomization is performed after screening and baseline evaluation, and eligible T2DM-CAP subjects will be randomized in a 1:1 fashion to receive 1 of 2 treatments. The group numbers are provided in continuously numbered, sealed envelopes made of carbonless paper. The envelopes will be held by a research administrator who will not be directly involved in the recruitment or follow-up of any participants. The administrator provides the subjects with their group number on the day of inclusion. Consequently, the subjects, clinical researchers, data managers, outcome assessors, and statisticians do not know the allocations, which not be revealed until the study is completed.

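### Section 3.8 tests baseline variables between randomised arms, which is uninformative, and its stated group comparison makes no use of pre-treatment severity for the binary day-14 effective rate: valid, but with some precision given up

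*Protocol article*

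**What the plan says.** All references are to the protocol article.

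- **Section 3.8 (Statistical analysis), baseline:** "For the sociodemographic data and baseline variables are conducted using analysis of variance and Chi-squared test". The same section adds "All statistical tests are bilateral tests" and sets significance at P below 0.05.
- **Section 3.8, efficacy:** paired t tests compare before with after within each group, and repeated measures ANOVA compares the two groups. No covariate is named. Chi-squared is named only for baseline data, and no test is assigned specifically to the effective rate.
- **Section 3.3.1 (Primary outcome):** total clinical effectiveness at day 14, a yes/no outcome formed by merging three of four response categories.
- **Section 2.5 (Randomization and allocation concealment):** randomisation follows screening and a baseline evaluation. SAS is used "to generate 92 random serial numbers"; no stratification factor is mentioned.
- **Section 2.3 (Recruitment):** the source is "All patients with T2DM-CAP at endocrinology department and respiratory department" of one hospital.
- **Section 3.3.2 (Secondary outcomes):** the pneumonia severity index is listed at days 4, 8 and 14. The text does not say that it is recorded at baseline, and Figure 1 is not available.

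**The concern.** Two things in section 3.8 are poorly chosen.

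First, a between-arm significance test on a baseline variable tests a hypothesis already known to be true when allocation is random: any difference arose by chance. A large P value does not show balance in a trial of this size, and a small one does not show faulty randomisation. Nothing in the section makes an analysis depend on the result, so the test only invites over-reading.

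Second, the named between-group method neither fits a binary outcome assessed once nor brings in pre-treatment severity. Baseline values exist before allocation. If severity predicts day-14 response, a prespecified adjusted comparison uses information that the stated one leaves aside. Power is already short here, because the sample size assumes a one-sided test while the analysis is two-sided. That mismatch is a separate matter, but it makes any recoverable precision worth more.

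**Working it through.** **1. The plan's own figure.** Section 2.4 states "we assumed the clinical effective rate of 73% in the control group and 93% in the experimental group over 14 days", with "single-sided type-1 error of 5% in both scenarios" and 80% power. The unpooled two-proportion formula gives, per arm,

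n = (0.73 × 0.27 + 0.93 × 0.07) × (1.645 + 0.842)² / 0.20² = 0.2622 × 6.185 / 0.04 = 40.5, so 41, or 82 in total.

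The section continues: "Assuming that 10% of patients are likely to be lost during follow-up, a total of 92 patients will be enrolled". 82 / 0.90 = 91.1, so 92. Both figures reproduce, and neither depends on covariate adjustment.

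**2. What a baseline test can show.** Assume that 40% of patients are in a more severe category (not in the documents), with 46 per arm. The SD of the difference between arms is √(0.4 × 0.6 × 2/46) = 0.102. A 15-point gap gives z = 0.15/0.102 = 1.47, P = 0.14: not significant, although a gap at least that large arises by chance in about 14% of trials.

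**3. Power with and without adjustment.** Inputs: 73% and 93% held as marginal rates; 41 per arm (evaluable) or 46 per arm (enrolled); two-sided 5%. The crude test is the chi-squared test. The adjusted test is the likelihood-ratio test in a logistic model with arm, one standard normal severity covariate and a two-level department that has no effect. The log-odds per SD of severity is assumed, from 0 to 2. There were 4,000 simulated trials per power setting.

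| Log-odds per SD | 41/arm: crude → adjusted | Gain | 46/arm: crude → adjusted | Gain |
|---|---|---|---|---|
| 0 | 71.8% → 72.3% | 0.5 | 76.9% → 76.4% | −0.5 |
| 0.5 | 71.7% → 73.3% | 1.7 | 75.4% → 76.9% | 1.5 |
| 1.0 | 71.7% → 77.6% | 5.9 | 75.7% → 80.7% | 5.0 |
| 1.5 | 71.3% → 81.2% | 10.0 | 76.4% → 86.2% | 9.8 |
| 2.0 | 71.4% → 86.4% | 14.9 | 76.1% → 90.0% | 13.9 |

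The Monte Carlo standard error of one power figure is about √(0.72 × 0.28/4000) = 0.7 points. A run of the model proposed below, with the standardised risk difference reported, gave gains of 0 to 2 points for a weak covariate and 6 to 10 points at log-odds 1.1 to 1.5.

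**4. Type I error.** With 83% in both arms (2,500 trials per setting), the crude test rejected in 4.1 to 5.7% of trials and the adjusted logistic test in 5.4 to 7.2%. The run of the proposed model gave 4.6 to 6.0% and 5.2 to 6.8%. A small part of the power gain therefore reflects a slightly liberal test. An adjusted linear model with HC3 standard errors kept null rejection at 3.6 to 5.1%. It lost 2.5 to 4.0 points against the crude test at log-odds 0 to 0.5, and gained about 1 point at 1.0 and 4 to 5 points at 1.5.

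**5. How many covariates the data can carry.** Expected ineffective patients: 41 × (0.27 + 0.07) = 13.9, or 46 × 0.34 = 15.6. The chance of none in the experimental arm is 0.93^41 = 5.1%, or 0.93^46 = 3.5%. Ordinary logistic regression then has no finite estimate for arm.

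**The case against.** The strongest reply is that this is a condensed article. It names no specific test for the effective rate and does not say that the comparison is unadjusted, and a full protocol or SAP may list covariates. That stands as a limit on the claim. The point rests on what section 3.8 does state: a method for baseline data and a method for comparing groups, neither of which is an adjusted comparison of a binary endpoint.

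The reply is also right about several stronger readings that a reader might infer and that the documents do not support:

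- **That chance imbalance makes the primary result wrong.** It does not. The unadjusted randomised comparison keeps its error rate near 5%, and its standard error already allows for chance imbalance. If severe patients responded 25 points less often (an assumption), the 15-point gap above would shift the difference in rates by 0.15 × 25 = 3.75 points. That is half the standard error of √(0.2622/46) = 7.5 points.
- **That baseline values serve only for significance tests.** Pre-treatment values also enter the within-group paired t tests, and possibly the repeated measures ANOVA.
- **That randomisation wrongly ignores department.** The article names no strata but does not rule them out. It gives no evidence that the two departments' patients differ, and all must meet the same eligibility criteria.
- **That a large loss of power is established.** The documents do not state the prognostic strength of severity, and the eligibility limits may narrow its range. The gain can be close to zero.

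**Conclusion.** The point holds in a limited form. The baseline tests are uninformative; removing them changes no efficacy result. The stated group comparison does not use pre-treatment severity for the primary outcome, so it is valid but may be less precise than it could be.

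The size is about 0 to 2 points of two-sided power at log-odds 0 to 0.5 per SD and about 6 to 10 points at 1.1 to 1.5, with 41 to 46 per arm. This rests on the protocol's 73% and 93%, on assumed prognostic strengths, on a roughly normal severity measure recorded before allocation, and on a logistic analysis. It also assumes that no full protocol or SAP already specifies adjustment. This is a worthwhile improvement, not the repair of an invalid analysis.

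**What to change.** 1. **Name the primary comparison.** Prespecify a logistic model for the day-14 effective rate with arm and one severity measure recorded before randomisation. The pneumonia severity index is the natural candidate if the full protocol confirms a baseline value. Department may be at most one further term.
2. **Report on the risk scale.** Give the standardised risk difference (predict every patient under each arm, average, subtract) with its 95% CI, and put the crude rates beside it.
3. **Name a fallback in advance**, such as penalised likelihood or the crude comparison, for the case where an arm has no ineffective patients (about 3 to 5% of trials).
4. **Drop the baseline P values** and describe baseline by arm.

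Stratifying the list by department is optional and does not correct an error.

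The cost is a few lines of analysis text. The statistical price is small: with 14 to 16 ineffective patients expected, covariates must stay at one or two, and null rejection may rise by about one point.
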